### **1.2 Secondary Objectives**

**Aim 2: When feasible to be delivered by staff activity personnel, explore the effectiveness of *On the Move* compared to a standard program; and sustainability compared to delivery by exercise leaders (when feasible). Explore barriers to identifying and training staff activity personnel.** *On the Move delivered by staff activity personnel (when feasible) will produce gains in above outcomes that are greater than the standard program; and comparable to when delivered by an exercise leader.*

**Aim 3: Explore the acceptability and the risks of the *On the Move* and standard exercise programs delivered by (a) exercise leaders and (b) staff activity personnel (when feasible).** *On the Move will result in greater satisfaction and higher attendance rates than the standard program. Attendance rates and satisfaction will be similar for exercise leader and staff activity personnel led programs when feasible to recruit staff personnel. Adverse event (falls, soft tissue injuries, muscle soreness, etc.) rates during exercise will be similar between the two groups and the two facilitators when feasible to recruit staff personnel.*

**Aim 4: Explore potential baseline predictors of benefit and risks of participation in *On the Move* program to facilitate informed patient decision making.** *We will be able to identify combinations of baseline physical, psychosocial and demographic factors associated with each of the treatment response and adverse events outcomes.*

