#### Summary

The evidence-based On the Move program was developed based on our past research and with input from older adults. In our initial pilot study, we demonstrate that the program is feasible and acceptable to the older adult and that activity staff personnel have confidence in their ability to lead the program. In our current pilot we demonstrate our ability to engage management from other community sites and the ability to recruit from different populations. The next key step is to examine the benefits and risks of the On the Move program in a larger, more diverse sample of older adults and to assess the sustainability of the program. Specifically, we are interested in determining if the challenging group-based program improves mobility and prevents functional decline and disability without any increased risk to the older adult and if the activity staff personnel can lead the On the Move exercise program obtaining similar results to the exercise leader delivered program.

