## **7 SAFETY ASSESSMENTS**

### **7.1 Expected Adverse Experiences**

1. Major risks such as a cardiac event or a fall are expected to be rare – expected to occur in less than 1% of people (less than 1 out of 100 people).(55) Gardner et al, 2000,(55) reviewed controlled clinical trials of exercise interventions for older adults at-risk for falling. No cardiac events or falls were reported in the 12 clinical trials reviewed. The at-risk older adults in the studies reviewed have slightly poorer physical performance than the older persons we expect to recruit for our study. In our recent MOBILE study, a 1 year cohort study of 120 older adults participating in 3 clinic visits over a 1 year period there were no cardiac events or falls reported. In all conditions of testing in which the

participant is standing and/or walking (eg conditions with a potential risk for falling), the participant will be directly supervised by the trained tester. The trained tester is present for all testing sessions. We expect this level of supervision reduces the risk of falling to an even greater degree.

2. Less severe risks of participation such as muscle soreness, fatigue, or minor sprains or strains with each assessment, are expected to be infrequent – expected to occur in 1-10% of people (1-10 out of 100 people). Gardner et al, 2000,(55) reviewed controlled clinical trials of exercise interventions for older adults at-risk for falling, finding reports of such side effects of the intervention reported in only 4 of the 12 studies reviewed. The side effects were not a reason for dropout from the study and were described as soreness or musculoskeletal symptoms, but no injuries.
3. There is a rare risk that confidentiality could be breached. All of the research records will be kept in a locked file cabinet and/or password protected files. All of the investigators and staff that assist with the management of the files are trained in the privacy and confidentiality regulations that govern research.

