### 9.2 Sample Size

We base our sample size justification on prior data from our RESTORE and PRIME pilot studies, two-tailed tests conducted at the  $\alpha=0.05$  level, a conservative attrition rate of 10% between baseline and follow-up assessments, practical consideration of a class size of 10 participants for group exercise, computational techniques that match our study design and proposed analytical approach as much as possible within the constraints of already published methodologies and commercially available sample size and power software (PASS 2002®, Number Cruncher Statistical Systems, Inc., Kayesville, Utah), and ability to detect differences that correspond to published meaningful change criteria(57) or moderate Cohen's effect sizes of  $d=0.5$ .(58)

The numbers needed to enroll in order to detect statistical significance of intervention effect when delivered by an exercise leader (Aim 1), are presented in **Table 1**. We take into account the clustering of participants by facility by assuming an intracluster correlation of 0.1 and a resulting design effect of 1.90 to appropriately inflate the sample size accordingly.(59) In

summary, a total of 280 participants with 140 in each arm will allow us to detect statistical significance in intervention effects in all main outcomes with at least 80% statistical power.

**Table 1. Number needed to enroll for detecting effects of intervention incorporating clustered design (x1.90), attrition (10%), and rounded up to class size of 10.**

| Outcome                    | Prior Information                |                                 |                                         | Estimated Sample Size                                   |                                 |
|----------------------------|----------------------------------|---------------------------------|-----------------------------------------|---------------------------------------------------------|---------------------------------|
|                            | Baseline Standard Deviation (SD) | SD in Baseline-Follow up Change | Meaningful Difference Targeted (Source) | Completers Needed Per Arm assuming No Clustering | Number Needed to Enroll Per Arm |
| LLFDI Overall Function     | 6.15                             | 4.86                            | 3.08 ( $d=0.5$ )                        | 41                                                      | 90                              |

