#### Aim 3(a):

We will fit a series of generalized estimating equations (GEE) models using the SAS® GENMOD procedure with each of the dichotomous adverse events, adherence (21+ sessions or  $\geq 90\%$ ) and satisfaction outcomes as the dependent variable; a binomial distribution for the outcome and a logit canonical link function; intervention arm, as the effect of primary interest; baseline value of outcome and any other measures found to be different between arms or deemed important as additional fixed effects covariates; and an exchangeable working correlation structure to account for clustering due to facility. We will appropriately construct contrasts to test hypotheses of differential proportions with adverse events based on intervention when delivered by exercise leaders.

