##### Aim 3(b):

will fit a series of generalized estimating equations (GEE) models using the SAS® GENMOD procedure with each of the dichotomous adverse events, adherence (21+ sessions or  $\geq 90\%$ ) and satisfaction outcomes as the dependent variable; a binomial distribution for the outcome and a logit canonical link function; intervention arm, delivery model and their interaction as effects of interest; baseline value of outcome and any other measures found to be different between arms or deemed important as additional fixed effects covariates; and an exchangeable working correlation structure to account for clustering due to facility. We will appropriately construct contrasts to test hypotheses of differential proportions with adverse events based on intervention when delivered by staff activity personnel and delivery mode.

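### Aim 3 hypothesises similar adverse event rates, but the only planned comparison is a test for a difference, and a non-significant result cannot support similarity

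*Supplement*

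**What the plan says.** All references are to protocol Version 2.0.

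- **Hypothesis (Section 1.2, Aim 3).** Adverse event "rates during exercise will be similar between the two groups and the two facilitators" where staff can be recruited. The aim itself opens with "Explore the acceptability and the risks of the" two programs, so it is worded as exploratory. The Summary closing Section 2 asks whether the program improves mobility and "prevents functional decline and disability without any increased risk to the older adult".
- **Analysis (Section 9.3.2, Aim 3(a)).** A binomial GEE model with logit link and an exchangeable working correlation "structure to account for clustering due to facility", used to "construct contrasts to test hypotheses of differential proportions with adverse events based on intervention" under exercise leaders. This sits under the heading for the main analysis.
- **Analysis (Section 9.3.3, Aim 3(b)).** The same model with delivery mode and the interaction added, to "test hypotheses of differential proportions with adverse events based on intervention" under staff delivery, and by delivery mode. This sits under the exploratory analyses.
- **Sample size (Section 9.2).** With 140 per arm the plan claims to detect "significance in intervention effects in all main outcomes with at least 80% statistical power". Tables 1 and 4 cover LLFDI, gait speed and six-minute walk distance. Adverse events do not appear.
- **Expected rates (Section 7.1).** Major events such as a fall or cardiac event are "expected to occur in less than 1% of people"; soreness, fatigue and minor sprains or strains in 1–10%.
- **Monitoring (Section 7.5).** Unblinded team members track whether event counts are unequal between groups. No criterion is given.

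**The concern.** The hypothesis and the test point in opposite directions. A difference test can give evidence that rates differ. When it does not reject, it says little unless power or precision is known to be good, and the plan gives neither for adverse events. It also names no margin or interval rule by which the analyst could judge that rates are similar.

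This matters here because On the Move is done mostly standing, with stepping and walking patterns, while Standard is done mostly seated. An excess of falls or strains is the obvious differential harm. The Précis says the findings will inform patient choice and could lead to wide adoption, so a safety statement resting on an uninformative test could travel far.

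**Working it through.** **Inputs.** From Section 9.2: 140 per arm, two-sided α = 0.05, ICC 0.1, class size 10, design effect 1.90, attrition 10%. From Section 7.1: base rates from below 1% to 10%. Assumed: these rates apply to the Standard arm, the design effect carries over to binary adverse events, and doubling and tripling serve as illustrative excesses, because the documents give no relevant difference.

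**Step 1, the plan's own figure.** Design effect = 1 + (10 − 1) × 0.1 = 1.90. For gait speed, n = 2 × (1.960 + 0.842)² × 0.20² / 0.10² = 62.8, so 63 by the normal formula and 64 with the t correction. This matches the stated 64 completers. Enrolment = 64 × 1.90 / 0.90 = 135.1, rounded up to 140, as stated.

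**Step 2, chance that the difference test misses an excess.** Effective n per arm = 140 / 1.90 = 73.7. With p̄ the mean of the two rates,

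power = Φ{ (|p₁ − p₂| − 1.96 × SE₀) / SE₁ }, SE₀ = √(2p̄(1 − p̄)/n), SE₁ = √((p₁(1 − p₁) + p₂(1 − p₂))/n).

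Example, 5% vs 10%, n = 73.7: SE₀ = √(2 × 0.075 × 0.925 / 73.7) = 0.0434; SE₁ = √((0.0475 + 0.0900) / 73.7) = 0.0432; (0.05 − 1.96 × 0.0434) / 0.0432 = −0.81; power 21%, miss 79%.

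| Standard vs On the Move | Missed, no clustering (n = 140) | Missed, design effect 1.90 (n = 73.7) | Same, with 10% attrition (n = 66.3) |
|---|---|---|---|
| 0.5% vs 1% (doubling) | 93% | 95% | 95% |
| 1% vs 2% (doubling) | 90% | 93% | 93% |
| 5% vs 10% (doubling) | 65% | 79% | 81% |
| 10% vs 20% (doubling) | 35% | 60% | 64% |
| 1% vs 3% (tripling) | 78% | 86% | 87% |
| 5% vs 15% (tripling) | 20% | 47% | 52% |
| 10% vs 30% (tripling) | 1% | 13% | 17% |

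With clustering, power for a tripling reaches 50% at a base rate of about 4.8% (5.2% with attrition). At the lowest rates the normal approximation flatters the test: with 1 event among 140 in Standard, Fisher's test needs 8 among 140 in On the Move (7 gives p = 0.066, 8 gives p = 0.036). For the staff-led comparison (60 vs 60), 10% vs 20% is missed 67% of the time without clustering and 80% with it.

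**Step 3, attainable precision.** With equal true rates, the 95% CI half-width for the risk difference is 1.96 × √(2p(1 − p)/n).

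| Event rate | n = 140 | n = 73.7 |
|---|---|---|
| 1% | 2.3 points | 3.2 points |
| 5% | 5.1 points | 7.0 points |
| 10% | 7.0 points | 9.7 points |

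**Step 4, could a margin be met?** For non-inferiority with equal true rates, one-sided 0.025 and 80% power, a margin equal to the base rate (ruling out a doubling) needs n = 2p(1 − p) × (1.960 + 0.842)² / p². That is 1555, 299 and 142 per arm at 1%, 5% and 10%, or about 3283, 632 and 300 enrolled after multiplying by 1.90 / 0.90.

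**The case against.** Several points on the other side stand.

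- **No decision rule is written.** A reader might infer that p > 0.05 will be taken as similar safety. The plan never says so. For Aims 1 and 2 it says that statistical significance will serve as the formal test; the Aim 3 text has no such sentence. The gap is a missing criterion, not a stated wrong one.
- **Aim 3 is worded as exploratory**, and 3(b) is placed among the exploratory analyses. Limited power is a lesser fault there. But 3(a) remains under the main analysis with contrasts described as hypothesis tests, and an exploratory aim suits estimation better than testing.
- **The base rates are borrowed.** The 1–10% in Section 7.1 is worded per assessment, whereas Aim 3 concerns events during exercise over 24 classes. If cumulative rates are higher, power for a given ratio is higher.
- **The ICC of 0.1 was set for the main outcomes.** A smaller value lowers the misses; the no-clustering column is the favourable bound.
- **Other safety reporting exists**: frequencies by arm (Section 9.3.1) and unblinded tracking (Section 7.5). Neither supplies a criterion for similarity.

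It is also tempting to say that any doubling or tripling would usually go unnoticed, or that a null result for falls is nearly certain whatever the true risk. The figures do not support either. A tripling from 10% is missed only 1–13% of the time, and 1% vs 10% only 9% without clustering and 33% with it.

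**Conclusion.** The concern holds in a bounded form. The plan states a hypothesis of similarity and offers only a difference test, with no margin, interval criterion or precision statement, so a non-significant contrast cannot support that hypothesis. This part needs no assumptions.

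The size does. With the Section 7.1 rates taken as Standard-arm rates and the design effect of 1.90 carried over, a doubling is missed more often than not across the whole range from below 1% to 10%. A tripling is missed more often than not only below about 5%, a range that includes falls and cardiac events if they are as rare as expected. Without clustering, a doubling from 10% is detected more often than missed. The documents show neither an intention to read non-significance as equal safety nor a trial blind to every large excess.

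**What to change.** 1. In Aims 3(a) and 3(b), report the facility-adjusted risk difference (On the Move minus Standard) with its 95% CI for each adverse event outcome. Use an exact or cluster-level interval when events are few, since the logit contrast may not be estimable with no events in an arm. Treat the delivery-mode comparison in 3(b) the same way.
2. State that a non-significant contrast will not be read as similarity, and that an excess up to the upper confidence bound is not excluded.
3. Reword the Aim 3 safety hypothesis as estimation of the difference.
4. Give the attainable half-widths: about 2, 5 and 7 points at rates of 1%, 5% and 10% without clustering, and about 3, 7 and 10 points with design effect 1.90.
5. If a claim of similar rates is still wanted, fix a margin before unblinding. Because Section 7.5 has the biostatistician tracking events unblinded, those who set it should not have seen counts by arm. Step 4 of the working shows that ruling out a doubling is beyond this sample size.

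The cost is wording and one interval per adverse event outcome, with no extra participants or data. The downside is a more cautious safety statement: for rare events similarity will probably not be claimable.

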#### 9.3.3 Aims 2, 3(b) and 4 exploratory Analyses

##### Aim 2:

We propose an analytic strategy with an exploratory philosophy for Aim 2 sustainability aim, because of the uncertainty surrounding our ability to recruit and train a staff activity person to lead a class safely and per protocol.

We will fit a series of linear mixed models using the SAS® MIXED procedure with baseline to follow-up change in each of the continuous outcomes (LLFDI function/disability, walking ability, other measures of mobility performance) as the dependent variable; intervention arm (standard/*On the Move*), delivery mode (by exercise leader/staff activity personnel) and their interaction as fixed effects of interest; baseline value of outcome and any other measures found to be different between arms or deemed important as additional fixed effects covariates; and a facility random effect to account for greater similarity of participants from the same facility compared to different facilities and resulting non-independence of observations within facility (ie. clustering). We will construct appropriate means contrasts to estimate difference in gains in the two interventions when delivered by staff exercise personnel (Aim 2 effectiveness hypothesis); and difference in gains attributable to *On the Move* intervention when delivered by exercise leaders and staff activity personnel (Aim 2 sustainability hypothesis). Statistical significance of the estimates will serve as formal tests hypotheses. We note that participants randomized to staff activity personnel had to wait 12 weeks since their baseline assessment and randomization to start the intervention, during which they may have changed; and that they underwent a second baseline assessment immediately prior to starting the exercise intervention. Therefore, we will repeat the above analysis using their second baseline assessment instead of the first one to assess the sensitivity of results.

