| LLFDI Disability Frequency | 6.35                             | 4.76                            | 3.18 ( $d=0.5$ )                        | 37                                                      | 80                              |
| Gait Speed (m/s)           | 0.13                             | 0.20                            | 0.10                       | 64                                                      | 140                             |
| 6MWD (m)                   | 62.0                             | 42.8                            | 50                         | 13                                                      | 30                              |

Our sustainability Aim 2 depends on whether we are able to train a staff activity person ready to lead a class safely and per protocol. Further, we do not have a priori data in sufficient detail that allows us to reliably estimate the likelihood of suitably training a staff activity person in each of the main type of facility. Thus Aim 2 is exploratory in nature and we will also focus on barriers to suitably training a staff activity person. We anticipate that we will enroll approximately 120 participants into Aim 2. The power available to detect a statistically significant difference in gains attributable to *On the Move* when delivered by exercise leaders and staff activity personnel (sustainability hypothesis – Aim 2) are in **Table 4**. Power is  $\geq 90\%$  for all outcomes except for gait speed when comparing *On the Move* to Standard when delivered by facility staff in which case power is 78%.

1029 **Table 4. Number needed to enroll for establishing sustainability of *On the Move*, incorporating clustered design**  
 1030 **(x0.90), attrition (10%), and rounded up to class size of 10.**

| Outcome                    | Prior Information                |                                 |                                         | Estimated Sample Size                                      |                                 | New Aim 2 Statistical Power with Anticipated N=140+140+60+60                |                                                                                       |

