|----------------------------|----------------------------------|---------------------------------|-----------------------------------------|------------------------------------------------------------|---------------------------------|-----------------------------------------------------------------------------|---------------------------------------------------------------------------------------|
|                            | Baseline Standard Deviation (SD) | SD in Baseline-Follow up Change | Meaningful Difference Targeted (Source) | Completers
Needed Per Arm assuming No Clustering | Number Needed to Enroll Per Arm | Facility Staff as Good as Exercise Leader in Delivering OTM?
N=140 vs 60 | OTM More Effective than Standard Even when Delivered by Facility Staff?
N=60 vs 60 |
| LLFDI Overall Function     | 6.15                             | 4.86                            | 3.08 ( $d=0.5$ )                        | 66                                                         | 70                              | 98%                                                                         | 93%                                                                                   |
| LLFDI Disability Frequency | 6.35                             | 4.76                            | 3.18 ( $d=0.5$ )                        | 60                                                         | 60                              | 99%                                                                         | 95%                                                                                   |
| Gait Speed (m/s)           | 0.13                             | 0.20                            | 0.10                       | 105                                                        | 110                             | 90%                                                                         | 78%                                                                                   |
| 6MWD (m)                   | 62.0                             | 42.8                            | 50                         | 21                                                         | 30                              | >99%                                                                        | >99%                                                                                  |

1031  
 1032  
 1033

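### Aim 2 judges staff delivery comparable by a difference test with no margin, so a non-significant result stands in for comparability

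*Supplement*

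**What the plan says.** All references are to protocol Version 2.0.

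- **Hypothesis.** Section 1.2 expects staff-led On the Move to give gains "comparable to when delivered by an exercise leader". The matching power column of Table 4 (section 9.2) asks "Facility Staff as Good as Exercise Leader in Delivering OTM".
- **Decision rule.** Section 9.3.3 (Aim 2) fits a mixed model to change from baseline and forms the leader-versus-staff contrast within On the Move. It then says "Statistical significance of the estimates will serve as formal tests hypotheses". No equivalence or non-inferiority margin appears, and nothing says what result would count as comparable.
- **Power.** Section 9.2 uses "two-tailed tests conducted at the" 0.05 level, 10% attrition and, for Aim 2, a design effect of 0.90. Table 4 gives 98%, 99%, 90% and >99% for 140 versus 60.
- **Clustering.** The only random effect is for facility.
- **Time window.** Change runs from the first baseline. The section acknowledges the 12-week wait in the staff arm and adds that "we will repeat the above analysis using their second baseline assessment instead of the first one" as a sensitivity check.
- **Use of the result.** Aim 4 (section 9.3.3) combines the two delivery modes and stratifies only if they differ.
- **Status.** Sections 9.2 and 9.3.3 call Aim 2 exploratory.

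**The concern.** The hypothesis is similarity, but the test can only show a difference. A non-significant result may mean that the two modes perform alike or that the data are too few to tell, and the plan has no rule to separate these readings. The staff arm is expected to hold about 60 On the Move participants, while Table 4 itself lists 110 per arm as needed for gait speed.

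Section 2 names sustainability as a main priority of the stakeholder. If staff-led classes are reported as comparable on weak evidence, facilities could adopt a delivery mode that has lost much of the benefit. The same inference would carry into Aim 4, where predictors of benefit are sought in the pooled group.

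**Working it through.** **Inputs from the protocol.** Leader 140, staff 60 (Table 4). Attrition 10%, so 126 and 54 completers. Two-sided 0.05. Design effect 0.90 = 1 − 0.1, from an assumed intracluster correlation of 0.1 and pairing by facility. SD of change and target: LLFDI function 4.86 and 3.08; LLFDI disability frequency 4.76 and 3.18; gait speed 0.20 and 0.10 m/s; six-minute walk distance 42.8 and 50 m. Pilot gait-speed advantage over standard exercise (RESTORE, section 2): 0.21 − 0.14 = 0.07 m/s.

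**Step 1: reproduce Table 4.** SE = SD × √[0.90 × (1/126 + 1/54)]. For gait speed this is 0.20 × √(0.90 × 0.02646) = 0.0309 m/s. Power ≈ Φ(target/SE − 1.96).

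| Outcome | 140 vs 60: recomputed (stated) | 60 vs 60: recomputed (stated) |
|---|---|---|
| LLFDI function | 98.4% (98%) | 93.5% (93%) |
| LLFDI disability frequency | 99.1% (99%) | 95.5% (95%) |
| Gait speed | 90.0% (90%) | 78.2% (78%) |
| Six-minute walk | >99.9% (>99%) | >99.9% (>99%) |

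The table reproduces. The column headed as an as-good-as question is therefore power to detect a difference.

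**Step 2: how often would a real loss be non-significant?** This is one minus the power at that loss, by the noncentral t distribution with the same SE.

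| Outcome | Full-target loss | Half-target loss |
|---|---|---|
| Gait speed | 10% (0.10 m/s) | 64% (0.05 m/s) |
| LLFDI function | 2% | 47% |
| LLFDI disability frequency | 1% | 42% |
| Six-minute walk | about 0% (50 m) | 4% (25 m) |

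For a gait-speed loss of 0.07 m/s, 0.07/0.0309 = 2.27 and the result is non-significant 38% of the time.

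**Step 3: what a margin rule would deliver.** The protocol gives no margin, so a range is shown. With no true loss, power ≈ Φ(margin/SE − 1.96) for gait speed. The larger design effects are assumptions: 1 + 9 × 0.05 = 1.45 and 1 + 9 × 0.10 = 1.90, for half or all of the correlation lying within classes of 10.

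| Margin (m/s) | Design effect 0.90 | 1.45 | 1.90 |
|---|---|---|---|
| 0.10 | 90% | 72% | 61% |
| 0.07 | 62% | 43% | 35% |
| 0.05 | 37% | 25% | 20% |

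Under this rule a true loss equal to the margin would pass only 2.5% of the time.

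**Step 4: class-level variance, a separate point.** Leader-led and staff-led participants of one facility attend different classes under different instructors. Variance between classes therefore enters the contrast, but the model has no term for it. A simulation of the planned facility-only model used 4,000 replicates, an assumed 14 facilities of which 6 also have a staff class, and 9 completers per class. With half to all of the 0.1 correlation at class level (assumed), the nominal 5% difference test rejected a true null about 10–14% of the time.

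**Step 5: time windows.** Staff-arm change covers about 12 + 12 = 24 weeks from the first baseline, against about 12 weeks in the leader arm. The documents give no figure for change during the wait, so no size or direction can be computed.

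**The case against.** Version 2.0 made Aim 2 exploratory, with no fixed sample size and staff delivery only where feasible, so little formal weight should rest on it. That limits the consequence but does not remove it: the section still calls the contrasts formal tests, Table 4 advertises 90% or more on the as-good-as question, and Aim 4 uses the result.

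The plan is also well powered against the losses it targets. This stands. A reader might infer that a loss of the full target would often pass as comparable; on the stated inputs that happens about 10% of the time for gait speed and 2% or less for the other outcomes. The weakness lies in smaller losses, and for the six-minute walk it is slight even at half the target.

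A reader might further infer that the missing class term and the waiting period make losses easier to miss. The documents do not support that. Omitting class variance makes the standard error too small, which mainly creates false differences. In the simulation a 0.05 m/s loss was non-significant 63–64% of the time under the planned model and 76–80% under a class-aware test. The waiting period could act either way: decline would make staff delivery look worse, while improvement or practice would hide a loss. The protocol discloses this and plans the second-baseline analysis.

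Nor is the first baseline simply the wrong choice. Delivery mode is randomized after baseline testing (section 9.1), so the first baseline precedes randomization and fits the intention-to-treat plan. The second matches the time windows, but people lost while waiting would not have it. Which one leads is a trade-off.

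**Conclusion.** The point holds as a missing margin and a missing rule for concluding comparability. On the protocol's own figures, a gait-speed loss equal to the pilot's whole advantage would be non-significant about 38% of the time and a 0.05 m/s loss about 64%; half-target LLFDI losses about 42–47%. These rest on the stated SDs, 10% attrition and full benefit from pairing. Section 9.1 makes that pairing conditional on finding suitable staff, so 0.90 is a favourable factor. The 0.07 m/s benchmark comes from one-to-one delivery in a pilot of 50 people and is only a guide.

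The class-variance point is a separate matter of interval width and false differences. Its 10–14% depends on an assumed share of the correlation lying at class level and on the assumed facility layout. The window point is a bias of unknown direction with a check already planned. Aim 1 is unaffected.

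**What to change.** 1. State in section 9.3.3 that comparability is concluded only if the 95% confidence interval for leader minus staff excludes a loss larger than a pre-set margin for that outcome. Otherwise report the result as inconclusive.
2. Justify each margin against the expected benefit over standard exercise. For gait speed this means below 0.07 m/s. Taking over the 0.10 m/s target would allow staff delivery to lose more than the pilot's whole advantage and still be called comparable.
3. Relabel the Table 4 column as power to detect a difference.
4. Add a facility-by-delivery-mode (class) random effect to the Aim 2 model.
5. Keep both baseline analyses and claim comparability only if it holds from each.
6. Let the Aim 4 pooling rest on a stated rule, not on the absence of a significant difference.

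These are changes of wording and one model term; no new data are needed. The cost is wider intervals and a harder claim. At design effect 0.90 and no true loss, gait-speed power is already only 62% at a 0.07 m/s margin and 37% at 0.05, and it falls further with class variance. An inconclusive result is likely, which suits an exploratory aim.
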